#### Epworth sleepiness scale

This questionnaire uses a Likert-type scale in which the respondent indicates the most appropriate number ranging from 0 = would never doze or sleep to 3 = high chance of dozing or sleeping based on a given situation. A score of 10 or more is considered excessive sleepiness [32].

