#### Adherence to CPAP

We will assess CPAP adherence using subjective and objective measures. A self-report scale will be used to track CPAP adherence at the end of the 6-month period. CPAP adherence is defined as the mean number of hours per day and days per week participants report using CPAP [35,36] (adherence: > 4 hours a night for 70% of the nights or no report of symptomatic complaints). Throughout the study, CPAP adherence data will be electronically monitored on a daily basis. Data will be downloaded directly from CPAP devices [37].

A complete list of measures and the data collection schedule is provided in Table 2.

**Table 2 T2:** Schedule to acquire study data

**Outcome measures**	**Baseline**	**First follow-up**^ **a** ^	**Second follow-up**
Sociodemographic and clinical variables	X		
Apnea-risk evaluation system questionnaire	X		
Epworth sleepiness scale		X	X
CES-D	X	X	
Apnea knowledge test	X	X	
Apnea beliefs scale	X	X	
Medical outcomes study short form 36	X		
Self-efficacy scale	X	X	
Change assessment scale	X		
Functional outcomes in sleep questionnaire	X	X	
Process variables	X	X	
*Post hoc* evaluation variables			X
Sleep variables (chart audit)		X	

^a^Follow-up outcome ascertainment is performed by the Data Manager at 6 months post-enrollment and at 6 months post-telephone intervention (TTI).

Cardio-metabolic measures are as follows. (1) Weight will be measured without shoes and using a validated digital scale. (2) Waist circumference will be measured by 1) locating the upper hip bone and the top of the right iliac crest, 2) placing the measuring tape horizontally around the abdomen at the level of the iliac crest (tape is snug without causing compression), and 3) measuring at the end of a normal expiration. (3) BP measurements will be taken following American Heart Association guidelines [38]. Using a BPTru automated BP monitor, five readings will be obtained while participants are seated comfortably for five minutes prior to measurement [39]; the average BP will be used as the BP index for each visit. (4) Following the National Cholesterol Education Program standard guidelines for total cholesterol measurement, we will use the Cholestech LDX Analyzer; whole blood from fingersticks will be used for the quantitative determination of HDL-C and FPG utilizing established formulation [40]. All measurements will be collected by trained clinical research staff.

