### Statistical analysis

To describe the characteristics of the study population, we will use measures of central tendencies and dispersion for continuous data; frequency distributions will be used for categorical data. Chi-square tests will be used to compare categorical data, and ANOVA will be used for continuous data. Relationships between mediators of adherence to recommended sleep apnea assessment and CPAP treatment will be examined using binary multivariate logistic regression analysis. The two main dependent measures will be: adherence to physician-recommended sleep assessment (yes versus no) and adherence to CPAP treatment (yes versus no). Candidate mediators will include sleep apnea knowledge, self-efficacy, readiness, and trust/rapport with the HE. Effects of sociodemographic and clinical factors will be adjusted in those analyses. Repeated-measures MANCOVA will be used to examine differences between baseline and follow-up measures (for example, waist circumference (WC), BP, HDL-C, FBG/HbA1c); age, sex, and sleepiness will be entered as covariates. MANCOVA is a robust technique that incorporates routines to account for heterogeneous variances, serial correlations, and variance inflation [41].

### Hypothesis 1

TTI will lead to higher rates of sleep apnea assessment at 6 months. A comprehensive assessment of sleep apnea will be defined by documentation of an appropriate medical and sleep history by a sleep clinician and a nocturnal polysomnographic study.

#### Analysis for hypothesis 1

Analysis will be performed on an intention-to-treat basis. All participants in the treatment arm will be assumed to have received the full dose of the telephone intervention and all participants in the attention-control arm will be assumed to have received no tailored intervention. Prior to testing for intervention effects, we will verify the comparability of the treatment and control arms with respect to all available demographic and personal data. T-tests and chi-square tests will be used for continuous and categorical variables, respectively. Thus, receipt of sleep apnea assessments within the 6-month period will be a binary outcome, yes or no. We will use logistic regression to estimate the odds associated with receipt of sleep apnea assessment contrasting the two study arms.

### Hypothesis 2

TTI will lead to higher adherence rates to recommended follow-up care (that is, CPAP use (> 4 hours a night for 70% of the nights)) post-diagnosis of sleep apnea.

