#### Analysis for hypothesis 2

The analysis plan is similar to that for hypothesis 1. The focus will be on adherence to recommended CPAP treatment. We will use logistic regression to estimate the likelihood of adhering to prescribed CPAP treatment after a diagnosis of sleep apnea was made.

### Hypothesis 3

Effects of the intervention in maintaining adherence will be sustained 6 months after active interventions and interventions will improve clinical outcome measures (WC, BP, HDL-C, and FPG/HbA1c).

#### Analysis for hypothesis 3

We will test the hypothesis that participants in the intervention arm will sustain gains from the initial interactions with the HE, leading to long-term adherence to recommended treatment and follow-up care. It is routinely recommended that participants with sleep apnea return for a follow-up visit after initiating treatments, during which adherence to treatment plan and improvement in sleep parameters is assessed. In our protocol, clinical outcomes (WC, BP, HDL-C, and FPG/HbA1c) will be ascertained post treatment. The analysis plan to test adherence at 6 months post-randomization is similar as for hypotheses 1 and 2; participants returning for a follow-up visit will be grouped as long-term adherents versus non-adherents. Chi-square tests and logistic regression analyses will be used. Repeated-measures MANCOVA will be employed to examine differences between baseline and post-intervention measures (WC, BP, HDL-C, and FPB/HbA1c). *Post hoc* comparisons between groups will be performed with Bonferroni corrections, where univariate results are significant. As required by assumptions governing the use of ANOVA, and since we expect the dependent variables to be modestly correlated, we will first examine their collinearity. Next, normality of the distribution of each measure will be examined and transformations will be performed for non-gaussian distributions. In exploratory analyses, we will determine whether mixed effect modeling would support ANOVA results.

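### The clinical-outcome MANCOVA adjusts for an unspecified sleepiness measure, and the only named sleepiness scale is scheduled only after randomisation

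*Protocol article*

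**What the plan says.** The Statistical analysis section of the protocol article sets the model for the clinical outcomes: "Repeated-measures MANCOVA will be used to examine differences between baseline and follow-up measures". It then states that "age, sex, and sleepiness will be entered as covariates". Neither that section nor the analysis for hypothesis 3 says which instrument supplies sleepiness or at which visit. The arms are compared within this model: "comparisons between groups will be performed with Bonferroni corrections, where univariate results are significant".

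The Measures section describes one scale that scores sleepiness, the Epworth: "A score of 10 or more is considered excessive sleepiness". In Table 2, which the protocol presents as the full list of measures and their timing, the row "Epworth sleepiness scale" has a blank baseline cell and a mark at both follow-ups. The footnote to Table 2 places those follow-ups 6 months after enrolment and 6 months after the telephone intervention, so both come after randomisation.

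On the choice of model, the protocol says that "MANCOVA is a robust technique that incorporates routines to account for heterogeneous variances, serial correlations, and variance inflation". Under hypothesis 3 it adds: "In exploratory analyses, we will determine whether mixed effect modeling would support ANOVA results".

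**The concern.** A covariate measured after randomisation is safe only if treatment cannot change it, or if it has no link to the outcome. Neither can be assumed here. The trial's rationale is that the intervention raises CPAP adherence and that treatment then improves the metabolic indices, and the analysis for hypothesis 3 refers to better sleep parameters once treatment has begun. Sleepiness at follow-up may therefore lie on the path from arm to outcome. Adjusting for it would remove whatever part of the effect acts through sleepiness. It would also let in bias from any unmeasured cause shared by sleepiness and cardiometabolic status. The resulting estimate would not be the effect of being randomised to the intervention.

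The model has a second difficulty. The protocol credits MANCOVA with a property that it does not have by itself, and keeps the more flexible mixed model as an exploratory cross-check.

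**Working it through.** The plan gives no figure to reproduce on this point. The check is a comparison of its sections, followed by an illustration of the mechanism.

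**1. What could sleepiness mean?** Candidates in the Measures section, Table 2 and the Study sites/population section:

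| Instrument | What the protocol says of it | Baseline | First follow-up | Second follow-up |
|---|---|---|---|---|
| Epworth | scores sleepiness; 10 or more is excessive | blank | X | X |
| ARES questionnaire | covers sleep patterns and daytime functioning; excessive daytime sleepiness of 65% is reported for the subset of 70 assessed with it | X | blank | blank |

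The Epworth is the natural reading because it is the only scale described as scoring sleepiness. ARES is a possible reading and is the one with a scheduled baseline value. The text permits either.

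**2. What follows if follow-up Epworth is used?** Take one follow-up visit, with outcome Y and sleepiness S in SD units and higher values worse. T is arm (0 or 1), S0 is baseline sleepiness, and U is an unmeasured shared cause.

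- S = 0.5 S0 + aT + cU + error, with within-arm variance 1
- Y = dT + bS + cU + error
- Total arm effect = d + ab
- Within-arm slope of Y on S = b + c²
- Arm coefficient after adjusting for S = (d + ab) - a(b + c²) = d - ac²
- Bias = -a(b + c²)

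The bias is zero when a = 0 (the arm does not change sleepiness) or when b + c² = 0 (sleepiness has no causal or confounded link to the outcome). If the intervention lowers sleepiness (a < 0) and more sleepiness goes with worse outcomes, the bias is positive and shrinks a beneficial (negative) effect.

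The values of a, b, c and d below are all assumptions, with d = -0.10. The last two columns are means over 1,500 simulated trials of 170 per arm, fitted by least squares.

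| a | b | c | Total effect d + ab | Formula, adjusted for S | Simulated, adjusted for baseline S0 | Simulated, adjusted for S |
|---|---|---|---|---|---|---|
| 0 | 0.3 | 0.5 | -0.10 | -0.10 | -0.094 | -0.095 |
| -0.1 | 0.3 | 0 | -0.13 | -0.10 | -0.130 | -0.098 |
| -0.1 | 0.3 | 0.5 | -0.13 | -0.075 | -0.129 | -0.073 |
| -0.2 | 0.3 | 0 | -0.16 | -0.10 | -0.153 | -0.095 |
| -0.2 | 0.3 | 0.5 | -0.16 | -0.05 | -0.163 | -0.053 |
| -0.5 | 0 | 0 | -0.10 | -0.10 | -0.102 | -0.102 |

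Adjusting for baseline sleepiness recovers the total effect in every row, within simulation error. Adjusting for follow-up sleepiness does so only in the first and last rows, where the bias formula gives zero.

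**3. How large could a be?** The documents do not say. The power section expects 47% against 35% to undergo sleep assessment, a difference of 12 percentage points. If only those extra 12% changed, and all were diagnosed and treated, then a = 0.12 x k, where k is the mean change in SD among them. So a = -0.1 needs k = 0.1/0.12 = 0.83 SD, a = -0.2 needs 1.67 SD, and a = -0.5 needs 4.17 SD. Better CPAP adherence among those diagnosed would enlarge a. Incomplete diagnosis or adherence would reduce it. The table therefore shows direction and mechanism; it does not forecast the bias in this trial.

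**4. The claim about MANCOVA.** Standard repeated-measures MANCOVA allows for correlation within a person, so that part of the sentence is defensible. It assumes the same covariance matrix in each group, so it does not by itself account for heterogeneous variances. It also needs every outcome at every visit. The glucose outcome, FPG or HbA1c depending on diabetes status, does not fit easily into one joint outcome vector, and Table 1 gives diabetes in 50.2% of the source registry.

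**5. Reach.** Sleepiness is named as a covariate only for the MANCOVA. Hypotheses 1 and 2 are tested by logistic regression, for which it is not named.

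**The case against.** The strongest reply is that the protocol never says the covariate is the Epworth. A reader might infer that the plan commits to adjusting for a post-randomisation mediator and that the clinical results will be biased. The documents do not support that. ARES is completed at baseline and appears to yield a daytime-sleepiness measure, so it is also wrong to say that no baseline sleepiness information is scheduled. The blank cell may be a slip. The Epworth is the only named questionnaire in Table 2 without a baseline mark, the Exit interviews section has participants repeat the baseline questionnaires, and Table 2 gives waist, blood pressure, lipids and glucose no follow-up rows although the Outcomes section schedules them. All of this stands, and it limits the point to an unspecified covariate whose natural reading is unsafe.

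On size, a difference of 12 percentage points in assessment leaves limited room for a large arm-level shift in sleepiness. That stands too, and no bias in clinical units should be quoted.

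On the model, one can say that the protocol does not state that incomplete cases will be dropped, that missing-data handling belongs in the analysis plan, and that unequal covariance matrices matter little with 170 per arm. It is fair that silence on missing data is no fault in an article, and none is alleged. The need for complete outcome vectors is a property of the chosen method, and the sentence on heterogeneous variances is incorrect however small its effect with equal arms.

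**Conclusion.** The point holds in a limited form. The clinical-outcome model adjusts for sleepiness without fixing the measure or visit, and the only named sleepiness scale has no baseline assessment in the published schedule. That mismatch is certain from the text. Whether it would bias the arm effect depends on three conditions that the documents do not settle: that follow-up Epworth is the score used, that the intervention changes it, and that it is linked to the outcomes. If all three hold, the likely direction is attenuation. Its size cannot be computed from the documents.

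Only the secondary clinical outcomes under hypothesis 3 are touched. The primary logistic comparison of sleep-assessment receipt is not affected. Separately, the statement that MANCOVA accounts for heterogeneous variances is wrong for the standard method, and the mixed model that the protocol already mentions is the better lead analysis.

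**What to change.** 1. State that only a baseline sleepiness measure may be a covariate, and name it: the ARES daytime-sleepiness item already collected at baseline. Otherwise drop sleepiness. State that follow-up Epworth does not enter any model for the arm effect. If a baseline Epworth was in fact collected and the blank cell is a slip, correct Table 2 and name that score. If it was not, starting now is too late for most participants: 311 of about 340 are randomised, which leaves about 340 - 311 = 29.
2. Make the mixed-effects model the main analysis for each clinical outcome, with arm by visit, adjustment for age and sex, and all randomised participants with available data. Keep MANCOVA as a sensitivity analysis.
3. Delete the claim that MANCOVA accounts for heterogeneous variances.

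The cost is a few sentences of analysis text, slightly more modelling work, and a coarser sleepiness covariate than a full Epworth score. No further data collection is needed.

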### Eligibility criteria

Eligible participants must: 1) self-report their race/ethnicity as black/African American; 2) be ≥ 18 years old; 3) diagnosis of metabolic syndrome; and 4) have a positive screening for sleep apnea, as measured by the Apnea Risk Evaluation System (ARES™) questionnaire [23]. Exclusion criteria include: 1) documented co-existing sleep problems; 2) documented illness or disability in which death is expected within two years of enrollment; 3) intent to relocate from the New York City area within one year following enrollment; 4) non-English speaking; 5) not accessible via telephone; 6) impaired cognitive or functional ability; and 7) another family member participating in the study. All participants will be asked to provide written informed consent before enrollment.

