### Outcomes

The primary outcome will be adherence to physician-recommended assessment and treatment for sleep apnea. The secondary outcomes will include 1) maintenance of recommended treatment at 6 months and at 12 months; 2) waist circumference; 3) lipid levels; 4) BP; and 5) FPG or HbA1c for those who have a DM diagnosis. Outcomes assessment will be conducted at baseline, and at 6- and 12-months post-randomization.

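### The metabolic outcomes are tested as baseline versus follow-up, with the arm comparison left post hoc and conditional, although hypothesis 3 claims an intervention effect

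*Protocol article*

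**What the plan says.** The Statistical analysis section of the protocol article describes the metabolic analysis twice. The general paragraph says "Repeated-measures MANCOVA will be used to examine differences between baseline and follow-up measures" and adds that "age, sex, and sleepiness will be entered as covariates". Under Analysis for hypothesis 3 it says "Repeated-measures MANCOVA will be employed to examine differences between baseline and post-intervention measures (WC, BP, HDL-C, and FPB/HbA1c". Arm appears in neither sentence. The only between-group step for these outcomes is post hoc: "comparisons between groups will be performed with Bonferroni corrections, where univariate results are significant". A mixed model is planned as an exploratory check on the ANOVA.

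The claim to be tested is causal. Hypothesis 3 states that "interventions will improve clinical outcome measures (WC, BP, HDL-C, and FPG/HbA1c", and the second secondary aim, at the end of the Background, is to assess treatment effects on the indices of the metabolic syndrome.

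On timing, Analysis for hypothesis 3 says "clinical outcomes (WC, BP, HDL-C, and FPG/HbA1c) will be ascertained post treatment", while the Outcomes section says "Outcomes assessment will be conducted at baseline, and at 6- and 12-months post-randomization".

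**The concern.** The randomised comparison is what supports a statement about the intervention, and here it is the subordinate step. The test that is named is a change over time.

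Such a change can arise in both arms without any effect of the telephone intervention. Entry requires a "diagnosis of metabolic syndrome", so some regression to the mean is possible. Under Data safety and monitoring, medication changes are recorded at follow-up visits, and participants without an identifiable primary-care physician are referred to clinics. If the pre-post result is taken as the test of hypothesis 3, which the wording allows, a shared change would count as success.

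The condition can also work the other way. If the univariate result that opens the gate is the time effect, a real difference between arms may never be examined.

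**Working it through.** **1. The text.** For hypothesis 1 the article specifies a logistic regression that contrasts the two arms, so it names the arm contrast where it means one. For the metabolic outcomes, both descriptions name the baseline-to-follow-up difference instead. The between-group step is stated, but as post hoc and conditional. That is a stated ordering of tests, not only missing model detail.

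**2. How often the pre-post test is significant with no arm difference.** The article gives no effect size, SD or power for these outcomes, so there is no figure to reproduce.

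- From the article: 170 per arm, so n = 340. Two-sided alpha of 0.05 is stated for the primary outcome and assumed here.
- Assumed: the same systolic fall δ of 2 or 3 mmHg in both arms; SD of change s of 12 or 15 mmHg; one follow-up time; complete data.
- Formula: z = δ / (s/√340), with power about Φ(z − 1.96). Here √340 = 18.44, so the standard error is 0.651 (s = 12) or 0.813 (s = 15).

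| Fall | s = 12 | s = 15 |
|---|---|---|
| 2 mmHg | z = 3.07, Φ(1.11) = 87% | z = 2.46, Φ(0.50) = 69% |
| 3 mmHg | z = 4.61, Φ(2.65) = 99.6% | z = 3.69, Φ(1.73) = 96% |

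A second calculation in SD units, with assumed baseline/follow-up correlation r of 0.5 to 0.7, agrees. A shared drift of 0.1 SD makes the pooled pre-post test significant 45% to 66% of the time, and 0.2 SD makes it 96% to 99.7%.

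**3. The arm comparison under the same drift.** Simulated as a two-sample t-test on change (5,000 runs per setting), it rejected in 4.6% to 5.6% of runs for drifts from 0 to 0.3 SD. Requiring the time effect to be significant first, and then the arm contrast, gave 4.4% to 5.6% at a drift of 0.2 SD. The two-step route is not inflated by shared drift.

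**4. What the gate costs if it is the time effect.** Assume a true change of −0.3 SD in the intervention arm, 0 in control, and r = 0.5. In baseline SD units the SD of change is √(2(1 − 0.5)) = 1.

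- Arm contrast: z = 0.3/√(2/170) = 0.3/0.1085 = 2.77, power about 79% (simulated 78%).
- Gate: pooled mean change is −0.15 with standard error 1/√340 = 0.0542, so z is again 2.77 and the gate opens 78% of the time.
- With equal arms the two statistics are independent, so both are significant about 0.78 × 0.78 = 61% of the time (simulated 61%).
- At r = 0.7 the simulated fall is smaller: 94.5% to 89.0%.

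**5. Timing.** One sentence ties ascertainment to the period after treatment; the Outcomes section sets baseline, 6 and 12 months from randomisation. Table 2 does not settle it, because no row names these measures.

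**The case against.** A repeated-measures MANCOVA followed by univariate tests and then post hoc group comparisons is a familiar sequence. It may imply that arm is a between-subject factor, and the univariate results could include a group-by-time test. A condensed article may leave that to the full protocol or SAP. This stands in part: the intended model may be sound. But neither description says so, and the word for groups is loose, since the same paragraph also divides participants into long-term adherents and non-adherents.

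Four stronger readings are tempting and should not be drawn.

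- A reader might take 69% to over 99% as the false-positive rate for an intervention effect. It is not. If the gate is the time effect, it is how often the gate would open; the planned next step is then a Bonferroni-corrected group comparison, which shared drift does not inflate. A false claim arises only if the pre-post result is itself read as the test.
- A reader might say that participants were chosen for abnormal values of every measure. Entry is on a syndrome diagnosis, in people drawn from a registry where dyslipidemia stands at 48.4% and obesity at 31.6% (Table 1). If the diagnosis came before a fresh baseline reading, regression to the mean is smaller.
- A reader might infer that only those who reach sleep care would have metabolic outcomes, about 0.47 × 170 = 80 against 0.35 × 170 = 60 at the planning rates. That needs a literal reading of one loose phrase. The Outcomes section contradicts it, and Data safety and monitoring provides examinations before and after the intervention for participants generally.
- A reader might stress opposite changes that cancel. With −0.2 and +0.2 SD the gate opens only about 4% of the time, but this needs the control arm to worsen as much as the other improves.

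**Conclusion.** The concern holds as a defect in how the test is stated. For a hypothesis about the intervention's effect, the article makes the pre-post difference the named test and leaves the arm comparison post hoc and conditional. Read that way, a shared change of 2 to 3 mmHg would look like support for hypothesis 3 about 69% to over 99% of the time. That rests on an assumed drift and an assumed change SD of 12 to 15 mmHg, for which the document gives no source.

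The loss of power from the gate (78% to 61%, or 94.5% to 89.0%) applies only if the gate is the time effect, and also rests on assumed values. The document does not show that the trial abandons the randomised comparison, because a group comparison is planned. The timing issue reduces to two statements that need to be reconciled. These are secondary outcomes, and the primary adherence analysis is not touched.

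**What to change.** State that each metabolic outcome is tested by the between-arm contrast at 6 and 12 months, in all randomised participants as allocated. This can be the follow-up value regressed on arm with adjustment for the baseline value, or the arm-by-time term. Remove any condition on a significant time effect, and report change within arms as descriptive only. Reconcile the ascertainment sentence under Analysis for hypothesis 3 with the 6- and 12-month assessments in the Outcomes section, so that it is plain that measurement does not depend on having been assessed or treated for sleep apnea.

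The cost is wording: the same planned data and the same family of models serve. The small downside is that a between-arm test is less likely to reach significance than a pre-post test.

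### Repeated-measures MANCOVA, rather than the mixed model already planned, is the main test of the secondary cardio-metabolic outcomes; in standard form it uses only complete records

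*Protocol article*

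**What the plan says.** The protocol article names one main method for the cardio-metabolic outcomes, which its Outcomes section lists as secondary. Under Analysis for hypothesis 3: "Repeated-measures MANCOVA will be employed to examine differences between baseline and post-intervention measures". The general Statistical analysis paragraph names the same method and adds that "age, sex, and sleepiness will be entered as covariates". It defends the choice thus: "MANCOVA is a robust technique that incorporates routines to account for heterogeneous variances, serial correlations, and variance inflation".

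The alternative appears at the end of the hypothesis 3 paragraph: "In exploratory analyses, we will determine whether mixed effect modeling would support ANOVA results".

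On timing, the Outcomes section says "Outcomes assessment will be conducted at baseline, and at 6- and 12-months post-randomization". On population, "Analysis will be performed on an intention-to-treat basis" stands under hypothesis 1. The link from hypothesis 3 back to that plan is worded for adherence only: "The analysis plan to test adherence at 6 months post-randomization is similar as for hypotheses 1 and 2". The article gives no expected dropout rate. It does not say whether incomplete cardio-metabolic records are excluded or imputed.

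**The concern.** A multivariate repeated-measures analysis in its standard form needs the full set of dependent variables and covariates for each participant. Someone who withdraws after month 6, or has one failed fingerstick at one visit, then contributes nothing, even to outcomes that were measured. The robustness claimed for MANCOVA concerns variances, serial correlation and variance inflation, and none of these covers incomplete records.

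Two features of the plan could thin the complete records further:

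- Sleepiness is a covariate, but Table 2 schedules the Epworth scale only at the two follow-ups. If that scale supplies the covariate, a missed follow-up removes it too.
- The glycaemic measure is "FPG or HbA1c for those who have a DM diagnosis", and Table 1 puts diabetes at 50.2% of the source registry. If FPG and HbA1c were entered as two dependent variables, few records would be complete.

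At stake are the precision of the secondary results and, if people leave for different reasons in the two arms, their direction. A mixed model keeps whatever was observed, and the plan already includes one, but in the lesser role.

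**Working it through.** The article states no figure for retention or for the size of effect on these outcomes, so there is none to reproduce. From the article come 340 participants, 170 per arm, and two-sided alpha 0.05 (Power and sample size calculations), with assessments at baseline, 6 and 12 months (Outcomes). Every missingness rate, SD and correlation below is an assumption.

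**1. Complete records.** Let w be the proportion who withdraw and m the proportion of participants missing at least one measure at a visit, independently over three visits. Complete records = 340 × (1 − w) × (1 − m)³.

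- w = 10%, m = 2%: 340 × 0.90 × 0.9412 = 288 (85%)
- w = 20%, m = 5%: 340 × 0.80 × 0.8574 = 233 (69%)
- w = 30%, m = 5%: 340 × 0.70 × 0.8574 = 204 (60%)

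**2. Precision.** For a simple two-arm comparison at 80% power, the detectable difference in SD units is (1.96 + 0.842) × √(4/N).

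- N = 340: 2.802 × 0.1085 = 0.30
- N = 288: 2.802 × 0.1179 = 0.33
- N = 204: 2.802 × 0.1400 = 0.39

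**3. Bias under a null effect.** The simulation used 4,000 trials of 170 per arm. Systolic BP had SD 18 mmHg and correlation 0.6 between any two of three visits. About 22% of each arm left after month 6. In the intervention arm, leaving followed a logistic function of the standardised 6-month change (slope 0.6 or 1.2, less improvement meaning more dropout). In controls it was random unless stated. A comparison of mean changes in completers stands in for the MANCOVA.

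| Selection | Completers, 6 months | Completers, 12 months | All observed data |
|---|---|---|---|
| None in either arm | about 0 | about 0 | about 0 |
| Intervention arm only | 2.0 to 3.5 mmHg | 1.0 to 1.7 mmHg | about 0 at both |
| Controls at half strength | 0.9 to 1.5 mmHg | 0.5 to 0.7 mmHg | about 0 at both |

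Figures are false benefits for the intervention arm, for slopes 0.6 and 1.2 (halved in controls in the last row).

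**4. Baseline-adjusted completers' analysis.** A separate null simulation used correlations of 0.7, 0.6 and 0.7, about 20% dropout, and dropout that depended on the 6-month value itself in the intervention arm. Bias at month 12 was 0.03 to 0.06 SD, or 0.03 × 18 = 0.5 to 0.06 × 18 = 1.1 mmHg. Type I error was 6.4% to 10.5%, against 4.9% without selection.

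**5. One follow-up only.** If the selection acts on the only follow-up value, a participant who drops out has a baseline and nothing else. The likelihood estimate is then still biased by 1.6 to 2.9 mmHg, against 2.0 to 3.5 in completers.

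**The case against.** The strongest reply is that deletion is inferred from the method's default. No sentence in the article says incomplete records are dropped, and MANCOVA can be run after imputation. Rules for missing data are what a condensed article commonly leaves to the full protocol or analysis plan, neither of which is shown. This stands. The lack of an imputation rule is not part of the point, and a reader might wrongly infer that the intention-to-treat principle cannot be met for these outcomes. Analysis of imputed data by assigned arm would meet it.

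A reader might also infer that dropout will differ by arm, because controls are offered the intervention only after the 12-month assessment. The article does not establish this. Controls may receive up to 10 calls, the same maximum as the intervention arm; the $100 at 6 months is not arm-specific; and no dropout figures are given. Counselling on barriers could just as well retain participants who are not improving. The simulation shows what could happen under selection that was assumed, and its all-data estimate is unbiased by construction, because dropout there depends only on observed values.

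The visit schedule also limits the remedy. Outcomes lists three time points, whereas Data safety and monitoring describes physical examinations once before and once after the intervention, so the number of cardio-metabolic measurements is unclear. Step 5 shows that with one follow-up most of the dropout bias would remain.

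Finally, these outcomes are secondary and the mixed model would be run anyway. That limits the weight of the point but does not remove it: the article does state which analysis leads, and the one it chose handles partial records less well.

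**Conclusion.** The point holds as a criticism of a stated choice. The article makes repeated-measures MANCOVA the main test of the secondary cardio-metabolic outcomes and a mixed model exploratory. Unless values are imputed, the main test is then a complete-record comparison.

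The loss of precision follows from any incomplete records. Under the assumed rates 204 to 288 of 340 remain, and the detectable difference rises from 0.30 SD to between 0.33 and 0.39 SD.

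Bias is conditional. It arises when dropout is related to earlier values differently by arm: about 2.0 to 3.5 mmHg at 6 months and 1.0 to 1.7 at 12 when selection is in the intervention arm only, less with similar selection in controls or with baseline adjustment, and none when dropout is unrelated to outcome. These are hypothetical sizes, not forecasts for this trial. The primary adherence results do not depend on this choice.

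**What to change.** Reverse the order of the two planned analyses in the Statistical analysis section and under Analysis for hypothesis 3:

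- **Main analysis:** a mixed-effects model for each cardio-metabolic outcome, including all randomised participants with any measurement, analysed as randomised, with arm by visit and the baseline value in the model.
- **Multiplicity:** apply the Bonferroni correction, which the plan already names for post hoc comparisons, across these outcomes. With four outcomes that would be 0.05/4 = 0.0125 each.
- **Supportive analysis:** the repeated-measures MANCOVA, stating whether it uses complete records or imputed data.
- **Visits:** state at which visits the cardio-metabolic measures are taken, since the benefit depends on it.

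The cost is wording only, because the mixed model is already planned. There are two downsides. Results come per outcome instead of from one joint test. If there is only one follow-up measurement, the gain is mainly that a participant is not lost for one missing measure, with little protection against dropout bias. Trial status reports 311 participants already randomised, so the change should be made and dated before outcome data are seen by arm.
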